**3 Methodology**

- 1. **Study design**

The NAPRUTI study consists of two trials: RCT-A and RCT-B. Premenopausal women will be included in RCT-A, postmenopausal women in RCT-B. Both trials are multi-center, randomized double blind clinical trials with a follow-up time of 15 months.

Both trials consist of two parts: part one deals with UTI recurrence (non-inferiority part); part two aims to show a difference with respect to the development of bacterial drug resistance.

- 1. **Study duration**

Both trials will recruit 280 women. Patient enrolment is anticipated to last 2 years. After randomization patients will be followed for 12 months during which they will receive study medication and 3 months afterwards (“wash-out”-period). Total study duration will be 48 months.

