**8 Statistical analysis**

**8.1 Power and sample size calculations**

### Non-inferiority part: It is known from clinical practice that many women are afraid of contracting resistant bacteria. For that reason they do not want to take antibiotic prophylaxis over an extended period of time. These women are even willing to take non-antimicrobial prophylaxis with a lower success rate in preventing UTIs compared to antimicrobial prophylaxis. Therefore, we accept a 10 percent lower success rate of the non-antibiotic compared to the antibiotic prophylaxis.

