### Based on an expected success rate in prevention of recurrent UTIs with TMP-SMX of 95% [2], measured success rates of 85% and 87% in the premenopausal women treated with cranberries [8], and postmenopausal women treated with lactobacilli [5], respectively, a type I error rate of 0.05 (alpha, one-sided) and a type II error rate of 0.20 (beta), 130 analysable women are needed for each of the four treatment arms.

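### Section 8.1 claims 80% power for the non-inferiority part, but on its own planning rates and 10-point margin the power at 130 women per arm is about 5% in RCT-A and 14% in RCT-B

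*Protocol*

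**What the plan says.** Section 3.1 makes UTI recurrence a non-inferiority question in both trials: "part one deals with UTI recurrence (non-inferiority part". Section 8.1 sets the tolerated loss: "Therefore, we accept a 10 percent lower success rate of the non-antibiotic compared to the antibiotic prophylaxis". The same section then lists the planning rates: 95% for TMP-SMX, and "measured success rates of 85% and 87% in the premenopausal women treated with cranberries [8], and postmenopausal women treated with lactobacilli [5], respectively". The error rates and the result follow: "a type I error rate of 0.05 (alpha, one-sided) and a type II error rate of 0.20 (beta), 130 analysable women are needed". The 130 applies to each of the four arms, so one figure serves both trials. With an allowance for loss to follow-up, recruitment is 140 per arm and 560 in total.

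**The concern.** A non-inferiority calculation needs two separate quantities: the margin, and the true difference that the planners expect. Power comes from the distance between them. Section 8.1 gives a margin of 10 and expected deficits of 95 − 85 = 10 points (RCT-A) and 95 − 87 = 8 points (RCT-B). The distance is therefore 0 and 2 points, far too little for 130 women per arm to give 80% power.

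This is the sample size justification for a primary objective. The ethics committee and later readers are told that the chance of missing true non-inferiority is 20%, under rates at which it is far larger or, in RCT-A, at which the treatment sits exactly on the limit. A trial that then failed to show non-inferiority could be misread as an adequately powered negative result.

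**Working it through.** **Inputs (all from section 8.1).** Control success 95%; index success 85% (RCT-A) and 87% (RCT-B); margin 10; one-sided alpha 0.05 (z = 1.645); power 80% (z = 0.842); 130 analysable per arm. Assumptions: the margin is absolute (percentage points), and the test compares two proportions, declaring non-inferiority when the one-sided 95% confidence limit excludes a deficit of 10 points.

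**Step 1: reproduce 130.** The one-sided sample size to detect a difference, with pooled variance under the null, is

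n = [1.645·√(2·p̄·q̄) + 0.842·√(pc·qc + pt·qt)]² / d²

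and the continuity correction gives n′ = (n/4)·[1 + √(1 + 4/(n·d))]².

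- 95% vs 85%: p̄ = 0.90, d = 0.10, n = 110.2, n′ = 129.5, which rounds up to 130.
- 95% vs 87%: the same formula gives n′ = 181.3.

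So 130 matches a test of difference for RCT-A. It does not fit RCT-B even on that basis. The formula contains no margin.

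**Step 2: non-inferiority power at 130 per arm.**

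Power = Φ( [margin − (pc − pt)] / SE − 1.645 ), with SE = √[(pc·qc + pt·qt)/130].

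- RCT-A: SE = √[(0.0475 + 0.1275)/130] = 0.0367. Power = Φ(0/0.0367 − 1.645) = 5.0%. Because the numerator is 0, no sample size changes this.
- RCT-B: SE = √[(0.0475 + 0.1131)/130] = 0.0351. Power = Φ(0.02/0.0351 − 1.645) = 14.1%.

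**Step 3: sample size for 80% power in RCT-B.** n = (1.645 + 0.842)² × 0.1606 / 0.02², about 2,480 per arm. RCT-A has no finite answer.

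**Step 4: sensitivity.**

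| Variation | RCT-A | RCT-B |
|---|---|---|
| Base case | 5.0% | 14.1% |
| Farrington-Manning score variance | 5.0% | 13.4% |
| Exact enumeration of the Wald rule | 5.6% | 15.2% |
| 140 per arm | 5.0% | 14.6% |
| Relative margin, 10% of 95% = 9.5 points | 3.7% | 11.2% |
| One-sided alpha 0.025 | 2.5% | 8.2% |

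**Step 5: what 130 per arm can do (formula of step 2, 10-point margin).**

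| True rates, control vs index | Power |
|---|---|
| 95% vs 95% | 98% |
| 90% vs 90% | 85% |
| 88% vs 88% | 80% |
| 85% vs 85% | 73% |
| 82% vs 82% | 67% |
| 95% vs 92.5% | 80% |
| 92% vs 91% | 83% |

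**The case against.** The best defence is that 85% is only the lowest acceptable rate (95 minus 10), with both arms expected to reach 95%. Power at 130 per arm would then be 98%. Three things stand against this reading.

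- Section 8.1 calls 85% and 87% measured rates. They track the results in section 1.2: 16% UTI incidence with cranberry, hence 84% success, and 87% success among lactobacilli-colonised women in the vaginal estriol trial.
- 87% is not 95 minus 10, so it cannot be the limit.
- With 95% in both arms, n = (1.645 + 0.842)² × 0.095 / 0.10² gives 59 per arm, so neither 130 nor a type II error of 0.20 follows.

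Some objections do stand. The text does not say whether the 10 percent is absolute or relative, so the scale is an assumption; either reading leads to the same conclusion. The origin of 130 is an inference from a numerical match, since the protocol names no formula.

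A reader might also infer that both trials were almost certain to fail. That is too strong for RCT-B, where the planning rates leave a 14% chance of success, and both power figures hold only under those rates. Nor do the documents show that 130 per arm is too small: step 5 shows adequate power under several other true rates. Those scenarios are illustrations, not rates the protocol supports.

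**Conclusion.** The stated type II error of 0.20 is wrong for the non-inferiority part of both trials. On the protocol's own rates, margin and alpha, power at 130 per arm is 5.0% in RCT-A and 14.1% in RCT-B. No variation examined exceeds about 6% and 15% respectively. The conclusion rests on taking 85% and 87% as the assumed true success rates, as the text presents them, and on a comparison of two proportions.

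The error lies in the justification. Whether 130 per arm is adequate depends on true rates that section 8.1 has yet to state and defend. It would be wrong to say that 80% power is reached only when both arms are at about 88%: higher common rates give more power, and so do some small deficits, such as 92% vs 91%.

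**What to change.** In section 8.1, state separately for RCT-A and RCT-B:

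- the margin and its scale (absolute or relative);
- the one-sided alpha;
- the assumed true success rate in each arm, with its basis.

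Replace the type II error claim with the non-inferiority power at 130 per arm under those rates. Say that power is 5% under 95% vs 85% and 14% under 95% vs 87%, and add a short table such as the one in step 5. Any summary sentence should give examples: 80% power holds, for instance, when both arms have a true success rate of about 88% or higher, or when the true deficit is at most about 2.5 points at 95% control success.

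The cost is a rewritten paragraph and a table. The restatement adds no patients. Its downside is that the stated power becomes conditional and less favourable.

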### Resistance part: For both trials, the power to detect a 15% difference in prevalence of TMP-SMX resistance (30% versus 15%) between “care as usual (control) groups” and the non-antibiotics groups is 78.8%. Allowing for about 10% loss to follow-up a total of 560 (4 x 140) patients will be included in the two trials.

- 1. **Data analysis**

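### Section 8.1 needs 130 analysable women per arm, but 140 enrolled leave 126 at the stated loss of about 10%; 140 covers a loss of only about 7%

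*Protocol*

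**What the plan says.** Section 8.1 (Power and sample size calculations) gives three linked figures.

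- **Requirement.** For the non-inferiority part, "130 analysable women are needed for each of the four treatment arms". This rests on a TMP-SMX success rate of 95%, on "measured success rates of 85% and 87% in the premenopausal women treated with cranberries" and postmenopausal women given lactobacilli respectively, and on "a type I error rate of 0.05 (alpha, one-sided) and a type II error rate of 0.20 (beta").
- **Resistance power.** For resistance of 30% against 15%, the stated power is 78.8%. No number per arm, alpha, sidedness or continuity correction is given for it.
- **Enrolment.** "Allowing for about 10% loss to follow-up a total of 560 (4 x 140) patients will be included in the two trials".

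Section 3 (Study duration) agrees with the total: "Both trials will recruit 280 women", that is 2 x 140 per trial. The protocol gives no other loss rate or inflation.

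**The concern.** The allowance for loss is there to turn a required analysable number into an enrolment number. Here the enrolment number, reduced by the stated loss, does not return the required number. Anyone monitoring attrition would take a loss near 10% as already covered, although the requirement is missed once loss passes about 7%. The power figures in the same section would then describe more women than the plan itself expects to analyse. There is little slack on either side: the non-inferiority figure sits just above 80% at 130 per arm, and the figure for resistance, also a primary endpoint, is already below 80%.

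**Working it through.** **Inputs, all from section 8.1 unless noted.** Required analysable: 130 per arm. Loss: about 10%. Enrolment: 140 per arm, 560 in total. Success rates: 95% against 85%. Alpha 0.05 one-sided, beta 0.20. Resistance: 30% against 15%, stated power 78.8%. The continuity correction, and the two-sided 0.05 for resistance, are my inference from the match in step 1.

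**Step 1. Reproduce the plan's own figures.** With per-arm number n, difference d and mean rate p̄, the continuity-corrected power is

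Φ{ [d − 1/n − z·√(2p̄(1−p̄)/n)] / √([p1(1−p1) + p2(1−p2)]/n) }.

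- *95% v 85%, one-sided 0.05 (z = 1.645), n = 130.* d = 0.10, 1/n = 0.00769, null SE = √(2 x 0.9 x 0.1/130) = 0.03721, alternative SE = √((0.0475 + 0.1275)/130) = 0.03669. The argument is (0.10 − 0.00769 − 0.06121)/0.03669 = 0.848, so power is **80.2%**. Solving the same formula for 80% power and rounding up gives 130, the stated number.
- *Resistance 30% v 15%, two-sided 0.05 (z = 1.960), n = 130.* d = 0.15, null SE = √(2 x 0.225 x 0.775/130) = 0.05179, alternative SE = √((0.21 + 0.1275)/130) = 0.05095. The argument is (0.15 − 0.00769 − 0.10152)/0.05095 = 0.801, so power is **78.8%**, the stated figure.

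Both stated figures therefore belong to 130 women per arm.

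**Step 2. Apply the stated loss to the stated enrolment.**

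- 140 x 0.90 = 126 per arm, 4 below 130. Overall, 4 x 126 = 504 against 4 x 130 = 520, 16 short.
- In reverse, 130/0.90 = 144.4, so 145 per arm, or 580 in total.
- The common shortcut of adding 10% to 130 gives 143, which is not 140 either.
- The loss that 140 can absorb is (140 − 130)/140 = 7.1%.

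| Loss | Left from 140 |
|---|---|
| 7% | 130.2 |
| 8% | 128.8 |
| 9% | 127.4 |
| 10% | 126.0 |

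**Step 3. Size of the effect, same formulas with n = 126.**

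| Comparison | n = 130 | n = 126 | Change |
|---|---|---|---|
| 95% v 85%, one-sided, corrected | 80.2% | 78.9% | −1.3 points |
| Resistance 30% v 15%, two-sided, corrected | 78.8% | 77.4% | −1.4 points |

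**Step 4. Sensitivity for a non-inferiority test as such.** The 95% v 85% calculation is a test of a difference. For a non-inferiority test with equal true success rates p, I assume an absolute margin of 10 points, one-sided 0.05 and no continuity correction. Power is Φ{0.10/√(2p(1−p)/n) − 1.645}. The protocol does not give a common rate, so p is an assumption, shown over a range:

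| Common success rate (assumed) | n = 130 | n = 126 |
|---|---|---|
| 85% | 73.0% | 71.8% |
| 90% | 85.1% | 84.2% |
| 95% | 98.0% | 97.7% |

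The change is 0.3 to 1.2 points. Whether power is above or below 80% depends on the assumed rate, not on the 4 women.

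**The case against.** Four things can fairly be said in the plan's defence.

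1. **The loss is only approximate.** Section 8.1 says about 10%, and 140 fits a loss of 7%, so this may be loose rounding. That lowers the weight of the point. It does not remove it, since 8% and 9% already leave fewer than 130, and 7% is a generous reading of about 10%.
2. **Women lost to follow-up are not all lost to the analysis.** Section 8.2.2 plans an intention-to-treat analysis and survival methods for resistance, in which a woman lost early still contributes censored time. Section 4.3 separates stopping study medication from stopping data collection, to limit missing data. This softens the practical effect. It does not repair section 8.1, which states its requirement as analysable women and its allowance as loss to follow-up.
3. **The choice of formula matters more than the shortfall.** Without the continuity correction, resistance power at 126 per arm is 81.8%, against 77.4% with it. That difference of about 4 points is some three times the effect of losing 4 women. This stands, and is why the point is minor. The corrected formula is used because it is the one that returns the plan's 78.8%.
4. **No decision turns on it.** The plan already accepted less than 80% power for resistance, and another 1.4 points would hardly have changed that. This also stands.

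A reader might go further and infer that the trial is underpowered or that 20 more women must be enrolled (580 instead of 560). The document does not support that: the shortfall is 4 women per arm at a loss given only approximately. Nor can one say in general that the shortfall takes non-inferiority power below 80%. That holds for the 95% v 85% calculation that yields 130, but at an assumed common rate of 90% or 95% power stays well above 80%, and at 85% it is below 80% even with 130.

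**Conclusion.** The point holds as a minor arithmetic inconsistency. A requirement of 130 analysable women, enrolment of 140 and a loss of 10% cannot hold together in any arm; the loss consistent with the other two is at most about 7%. Taken at 10%, the plan loses 4 analysable women per arm and 1.3 to 1.4 percentage points of power on the formulas that return its own figures. The arithmetic on 126 and 7.1% needs no assumption beyond reading the loss as 10%. The power figures rest on the continuity correction and, for resistance, on a two-sided 0.05 test, neither of which the protocol states, and they count every woman lost as contributing nothing to the analysis. The trial's validity is not in question; what needs correcting is the attrition it can tolerate and the number to which its power refers.

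**What to change.** Keep 560 women and amend section 8.1 in one of two ways:

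- state that 140 per arm allows for about 7% loss to follow-up, leaving the 130 and both power figures as they are; or
- keep the loss at about 10% and state that 126 analysable women per arm are then expected, with power of 78.9% for 95% against 85% (one-sided 0.05, continuity-corrected) and 77.4% for resistance (two-sided 0.05, continuity-corrected).

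If a non-inferiority power at equal success rates is added, label the common rate as an assumption and show the range rather than a single value.

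The cost is one or two sentences in section 8.1. No extra patients are needed, and enrolment, follow-up and analysis do not change.

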**8.2.1 General approach**

The data-analytic approach involves data-quality management and data-analysis. Flawless data-files will be ensured by double data-entry procedures. Data-analysis proper will follow four steps: (1) univariate data checks to assess distributions and identify potential outlying values, (2) relevant bivariate analyses using tables and scatter plots, to assess crude associations between co-variables and the outcomes, and among co-variables, (3) stratified analyses and Kaplan-Meier analysis aimed at the treatment effects, (4) (Cox) regression models.

**8.2.2 Primary outcome**

Data will be analysed according to the intention to treat principle. In the two trials, the (cumulative) proportions of symptomatic UTIs at 12 months will be compared between the groups (non-inferiority part), and the time intervals to the first occurrence of faecal and urine antibiotic resistance will be compared between the two groups using standard survival time analysis techniques (resistance part).

- - 1. **Secondary outcome**

Data differences between the proportions showing adverse effects at 12 months will be analysed similarly as the primary ones, except the quality of life measures at 12 months, for which multivariable linear regression will be used. Since antibiotic resistance is a gradual phenomenon, a more refined analysis using ordinal logistic regression, will assess differences in proportions of patients at different concentrations of antibiotic resistance between the treatment groups. Other secondary analyses pertain to all microbiological outcomes at 15 months.

In both trials we will also separately analyse the patients with uncomplicated versus complicated UTIs.

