**2 Study objectives and endpoints**

**2.1 Study objectives**

**2.1.1 Primary objectives**

- To determine if non-antibiotic prophylaxis is a non-inferior treatment in the prevention of recurrent symptomatic UTIs compared to the currently standard antibiotic prophylaxis in pre- and post-menopausal women (non-inferiority trial)
- To assess if non-antibiotic prophylaxis reduces the selection of antibiotic resistant micro-organisms in urine and faeces compared to currently standard antibiotic prophylaxis in pre- and postmenopausal women
  - 1. **Secondary objectives**
- To evaluate if non-antibiotic prophylaxis compared to antibiotic prophylaxis in pre- and post-menopausal women lead to differences in the:

- incidence of asymptomatic bacteriuria

- incidence of other (non-urinary tract) infections

- incidence of adverse events

- quality of life

- To evaluate the costs and cost-effectiveness of non-antibiotic prophylaxis compared to antibiotic prophylaxis in the prevention of recurrent UTIs in pre- and post-menopausal women.

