**2.2 Study endpoints**

**2.2.1 Primary endpoints**

- the numbers of recurrences of symptomatic UTI

- time to first occurrence of antibiotic resistance in urine or

faeces

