**4.3 Withdrawal from study**

Following enrolment, participants may discontinue study participation for the

following reasons:

- Voluntary withdrawal.

- Withdrawal requested by one of the investigators or the treating physician.

Strict distinction is made between withdrawal of study medication (non-adherence) and willingness to participate in data collection efforts. This approach will likely reduce the number of missing data values and facilitate a proper intention-to-treat analysis.

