**5.5 Compliance checking method**

The compliance will be measured monthly (together with the collection of the vaginal swabs and urine and faeces samples) by pill counts. In addition, vaginal and faecal cultures will be examined on the presence of lactobacilli, and urine concentrations of TMP-SMX and proanthocyanidins will be determined.

1. **Clinical and laboratory evaluations**
   1. **Clinical evaluations**

During the course of the study, a set of Case Report Forms (CRFs) is completed. At t= 0 (at inclusion) demographic data (age, place of residence [for example nursing home], sexual activity, relevant medical history and concomitant diseases, number of UTIs in the previous year, medication, known urinary tract abnormalities, urinary catheter use) will be collected by the study coordinator.

Each month thereafter, during the 15 months of follow up, a questionnaire is sent to the patient. On those questionnaires, other relevant parameters concerning possible adverse events (e.g., allergic reactions, skin rash, gastrointestinal disturbances), possible interactions with other medication, and the medical history (change of place of residence, new concomitant diseases, medication change, pregnancy, hospital admissions, invasive procedures, operations, urinary catheter placement or removal) during the follow-up will be noted.

Quality of life questionnaires (concerning the general well-being and related to the disease) will be administered at baseline and 6, 12 and 15 months post-randomization.

- 1. **Laboratory evaluations**

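### Intention to treat is the only analysis principle the protocol names for the non-inferiority comparison; some forms of non-adherence then favour the claim, and the compliance data feed no stated analysis

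*Protocol*

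**What the plan says.** The first primary objective (protocol section 2.1.1) is to "determine if non-antibiotic prophylaxis is a non-inferior treatment in the prevention of recurrent symptomatic UTIs" relative to antibiotic prophylaxis. Section 8.1 sets the tolerated deficit: "we accept a 10 percent lower success rate of the non-antibiotic compared to the antibiotic prophylaxis".

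Section 8.2.2 opens the primary analysis with "Data will be analysed according to the intention to treat principle". It then names two comparisons under that principle: the 12-month proportions for the non-inferiority part, and time to first resistance for the part meant to show a difference. Section 4.3 separates stopping study drug from leaving data collection, and explains: "This approach will likely reduce the number of missing data values and facilitate a proper intention-to-treat analysis".

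Section 5.5 states "The compliance will be measured monthly", by pill counts, supported by cultures and urine concentrations. Section 6.1 has monthly questionnaires that record medication changes. Sections 8.2.1 to 8.2.3 use none of this in an analysis, and no per-protocol or other adherence-based set appears in the protocol.

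**The concern.** One analysis principle serves two questions on which dilution acts in opposite directions. When non-adherence makes the arms more alike, a test for a difference loses power, which is the safe direction. A non-inferiority test gains, because a smaller observed deficit is easier to place inside the margin.

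The protocol itself makes one harmful pattern plausible. Section 1.2 says that many women are reluctant to take antibiotic prophylaxis for long. Section 7.1 lists gastrointestinal, vaginal and skin reactions for the antibiotic, while it describes cranberry as very safe and reports no adverse events for the lactobacilli. Section 7.2 allows study drug to be stopped for a possibly related event. Tablet and capsules are distinguishable (section 3.3.2), so a woman can drop one and keep the other. If women on active co-trimoxazole drop the tablet, the reference arm loses its protection and the index product looks closer to it than it is.

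At stake is the error rate of the main efficacy claim, in a plan with no stated second analysis that would show the problem.

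**Working it through.** **Inputs from the protocol.** Section 8.1 gives control success 95%, cranberry success 85%, a 10-point margin (read as absolute), one-sided alpha 0.05 and 130 analysable women per arm. The pair 95% vs 85% is the protocol's own planning assumption for RCT-A and lies exactly at the margin, so it is the natural point at which to examine the type I error.

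**Reproducing the 130.** The one-sided two-proportion formula gives [1.645·√(2·0.90·0.10) + 0.842·√(0.95·0.05 + 0.85·0.15)]² / 0.10² = 110.2. The continuity correction gives (110.2/4)·[1 + √(1 + 4/(110.2·0.10))]² = 129.5, hence 130. This formula is for detecting a difference. Whether it suits a non-inferiority aim is a separate matter, and only n = 130 is carried forward.

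**Assumptions, not in the protocol.** The shares of 10% and 20% are illustrative. Women without active prophylaxis are given 64% success, from the 36% six-month UTI incidence in untreated controls of the cranberry trial described in section 1.2. The non-adherence is taken to hold from the start.

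**Formula.** With control success pC and index success pI as they appear under intention to treat, d = pC − pI and SE = √{[pC(1 − pC) + pI(1 − pI)]/130}:

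P(declare non-inferior) = Φ[(0.10 − d)/SE − 1.645].

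With full adherence, d = 0.10 and the result is Φ(−1.645) = 5.0%.

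**Effect of each pattern on the arms (share f).**
- Control women stop the tablet: pC = 0.95(1 − f) + 0.64f; pI = 0.85.
- Both arms stop everything: pC as above; pI = 0.85(1 − f) + 0.64f.
- Index women take antibiotic prophylaxis before any UTI: pC = 0.95; pI = 0.85(1 − f) + 0.95f.
- Index women stop only the capsules: pC = 0.95; pI = 0.85(1 − f) + 0.64f. Capsules are placebo in the control arm, so stopping them there changes nothing.

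| Pattern | f | pC | pI | d | SE | P(non-inferior) |
|---|---|---|---|---|---|---|
| Control stops tablet | 10% | 0.919 | 0.850 | 0.069 | 0.0394 | 19.5% |
| | 20% | 0.888 | 0.850 | 0.038 | 0.0418 | 43.6% |
| Both arms stop everything | 10% | 0.919 | 0.829 | 0.090 | 0.0408 | 8.1% |
| | 20% | 0.888 | 0.808 | 0.080 | 0.0443 | 11.6% |
| Index takes antibiotic | 10% | 0.950 | 0.860 | 0.090 | 0.0359 | 8.6% |
| | 20% | 0.950 | 0.870 | 0.080 | 0.0351 | 14.1% |
| Index stops capsules only | 10% | 0.950 | 0.829 | 0.121 | 0.0382 | 1.4% |
| | 20% | 0.950 | 0.808 | 0.142 | 0.0395 | 0.3% |

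Example, second row: (0.10 − 0.038)/0.0418 = 1.484; 1.484 − 1.645 = −0.161; Φ(−0.161) = 43.6%.

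**Sensitivity to the 64%.** If stoppers have 80% success instead, 20% stopping of the control tablet gives pC = 0.8·0.95 + 0.2·0.80 = 0.92, d = 0.07, SE = 0.0393 and Φ(0.763 − 1.645) = 18.9%. The size depends strongly on this value; the direction does not.

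**A product 15 points worse (95% vs 80%).** At a 20% share the same formula gives 8.4% (control stops tablet), 1.9% (both stop everything) and 1.5% (index takes antibiotic), against 0.2% with full adherence. At 30% the figures are 23.5%, 4.0% and 3.8%.

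**The case against.** The strongest reply is that the protocol does not say intention to treat is the only analysis. Analysis sets and supportive analyses are often left to the SAP, which may add a per-protocol set and use the compliance data. That stands to this extent: a reader might infer that no such analysis exists, and the protocol cannot show that. What it does show is that the primary analysis of a non-inferiority claim has been chosen, with no condition on the claim beyond it.

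A reader might also infer that intention to treat favours non-inferiority whenever women stop treatment. The double-dummy design (sections 3.3.2 and 5.2) does not support this. Stopping capsules removes active treatment from the index arm alone and widens the deficit, so a false claim becomes rarer.

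Nor does a change of prophylaxis after a recurrence dilute the analysed endpoint. Section 8.2.2 says that "proportions of symptomatic UTIs at 12 months will be compared between the groups (non-inferiority part"), and such a woman has already counted as a failure. The argument would return only if the analysis used the endpoint as listed in section 2.2.1, "the numbers of recurrences of symptomatic UTI".

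The shares and the 64% are assumptions, and under index-arm switching or general stopping a product 15 points worse still passes in under 5% of trials at a 30% share. That reassurance does not extend to stopping of the control tablet.

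Finally, intention to treat estimates a legitimate quantity, the effect of assignment, and the rates above are false only relative to the effect under adherence. That is fair. But a small deficit produced by a reference arm not taking its drug is weak support for replacing that drug.

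**Conclusion.** The point holds as a weakness in a stated analysis choice. Intention to treat alone does not protect the non-inferiority claim, because the direction of its bias depends on which component women drop and when, and no stated analysis would reveal which pattern occurred. For a product exactly at the margin, an assumed 10% to 20% share moves the nominal 5% anywhere from 0.3% to 43.6%. The upper end comes from stopping the control tablet, the pattern the protocol's own background makes plausible.

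The magnitudes rest on assumed shares, on 64% success without prophylaxis, on non-adherence from the start and on a normal approximation. Later stopping would have less effect. The documents do not support saying that the error rate is in fact inflated in this trial, or that every departure from treatment inflates it.

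**What to change.** Keep intention to treat and add a per-protocol analysis of the 12-month proportion. Define its set in writing before unblinding, from the section 5.5 compliance data (tablet and capsules separately) and the medication changes on the monthly questionnaires of section 6.1. Judge adherence over the months before a first UTI, so that stopping in response to a recurrence does not remove a failure from the set. State that non-inferiority is claimed only if both analyses exclude a 10-point deficit at the one-sided 5% level. Leave the resistance part, which seeks a difference, on intention to treat.

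The cost is a few sentences and one further analysis, mostly of data already planned. Check that the questionnaires capture non-prescribed cranberry and probiotic use, which section 6.1 does not name. The claim becomes slightly harder to make. The per-protocol set is smaller and not fully protected by randomisation, and can itself be biased in either direction, which is why it supplements intention to treat and does not replace it.

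### Section 8.1 treats the 10-point non-inferiority margin as a difference to detect, and section 8.2.2 never ties the margin to the analysis

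*Protocol*

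**What the plan says.** Section 2.1.1 makes non-inferiority the first primary objective: "To determine if non-antibiotic prophylaxis is a non-inferior treatment in the prevention of recurrent symptomatic UTIs".

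The non-inferiority part of section 8.1 sets the margin: "we accept a 10 percent lower success rate of the non-antibiotic compared to the antibiotic prophylaxis". It then takes a success rate of 95% on co-trimoxazole, 85% on cranberries (RCT-A) and 87% on lactobacilli (RCT-B), and concludes that with "a type I error rate of 0.05 (alpha, one-sided) and a type II error rate of 0.20 (beta), 130 analysable women are needed" in each of the four arms.

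For the analysis, section 8.2.2 specifies intention to treat and says that "the (cumulative) proportions of symptomatic UTIs at 12 months will be compared between the groups (non-inferiority part"). Section 8.2.1 lists stratified, Kaplan-Meier and Cox analyses as a general approach for all outcomes. Neither section mentions the margin, the one-sided alpha, a confidence bound or a criterion for concluding non-inferiority.

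**The concern.** A non-inferiority test takes as its null hypothesis that the new treatment is worse by at least the margin. Alpha then limits the chance of accepting a treatment that is exactly that much worse, and power is calculated at an assumed true difference smaller than the margin.

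Section 8.1 does not do this. It enters the control rate and a rate 10 points lower as the expected results in RCT-A, so the assumed true deficit equals the margin. In RCT-B the assumed deficit is 8 points, close to the margin. No sample size gives 80% power to show non-inferiority when the truth lies on the margin. The quoted 130 must therefore come from a different hypothesis.

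Two things are at stake. The first is what the 80% power means. The second is which error the analysis controls: in a test of no difference, alpha guards against falsely declaring a deficit, and the risk of overlooking a margin-sized deficit is beta. Because 8.2.2 leaves the comparison open, nothing in the protocol corrects the hypothesis that 8.1 started from.

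**Working it through.** **Inputs (section 8.1).** Control success 0.95; non-antibiotic success 0.85 (RCT-A) and 0.87 (RCT-B); one-sided alpha 0.05 (z = 1.645); power 0.80 (z = 0.842); 130 analysable women per arm. The 10 percent is read as percentage points, which fits 95% v 85%.

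**1. Reproducing 130.** For a test of equal proportions,

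n = [1.645·√(2·p̄(1−p̄)) + 0.842·√(p₁(1−p₁) + p₂(1−p₂))]² / (p₁−p₂)²

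With p₁ = 0.95, p₂ = 0.85 and p̄ = 0.90, n = 110.2. The continuity correction, n/4·[1 + √(1 + 4/(n·0.10))]², gives 129.5, that is 130. The same formula at 95% v 87% gives 182, so 130 matches the RCT-A rates only.

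**2. Cross-check.** Section 8.1 also quotes 78.8% power for resistance at 30% v 15%. A continuity-corrected test of no difference (two-sided 0.05, 130 per arm) gives 78.8%. The same type of formula appears to lie behind both parts.

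**3. What a margin-based calculation gives.** With margin 0.10 and true deficit d = p₁ − p₂,

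n = (1.645 + 0.842)²·[p₁(1−p₁) + p₂(1−p₂)] / (0.10 − d)²

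power at 130 = Φ[(0.10 − d)/SE − 1.645], where SE = √{[p₁(1−p₁) + p₂(1−p₂)]/130}

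| True rates | d | SE | n per arm for 80% | Power at 130 |
|---|---|---|---|---|
| 95% v 85% (8.1, RCT-A) | 0.10 | 0.0367 | none | 5% |
| 95% v 87% (8.1, RCT-B) | 0.08 | 0.0351 | 2483 | 14% |
| 95% v 95% (assumed here) | 0 | 0.0270 | 59 | 98% |
| 90% v 90% (assumed here) | 0 | 0.0372 | 112 | 85% |

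The RCT-B power is Φ(0.02/0.0351 − 1.645) = Φ(−1.076) = 14%. Full enumeration of the two binomials at 130 per arm gives 5.6%, 15.2% and 97.4% for the first three rows, so the normal approximation is adequate.

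**4. Error rate at the margin.** By full enumeration with true rates of 95% v 85% and 130 per arm, the one-sided 0.05 test of no difference is non-significant in 12.6% of trials uncorrected and 18.5% with the continuity correction used in the sample size. At 126 per arm (140 less 10%), these become 13.5% and 19.9%. The rule that the observed deficit + 1.645·SE must be below 0.10 accepts in 5.6% of trials at 130 per arm and 5.8% at 126.

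**5. Example.** Suppose 124/130 and 117/130 women succeed, a deficit of 5.4 points. The continuity-corrected one-sided test gives p = 0.076, which is not significant. The one-sided 95% upper bound of the deficit is 10.7 points, so non-inferiority is not shown.

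**The case against.** The strongest reply is that a protocol may leave the interval method and the decision sentence to a statistical analysis plan, which is not at hand. The protocol fixes the objective, the margin and its direction, and a one-sided alpha. Section 8.2.2 labels the comparison as the non-inferiority part, and section 3.1 assigns the search for a difference to the resistance part only. A planning formula does not dictate the analysis.

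Most of this stands. A missing decision sentence alone would be a weak point. A reader might infer that the protocol plans to accept non-significance as proof of non-inferiority, but no passage says so, and section 3.1 points the other way. A reader might also infer that the primary test must be one of no difference because section 8.2.3 analyses adverse effects like the primary outcomes. That does not follow: one confidence interval for a difference in proportions can be read against −10 points for one outcome and against zero for another.

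A size near 130 also arises from a non-inferiority formula with equal rates (131 at 88% uncorrected, or at 90% with continuity correction), but the protocol states neither pair. It states 95% with 85% and 87%, and the first pair reproduces 130.

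The reply does not remove the sample-size construction. The text of 8.1 presents the calculation as the non-inferiority part, and its figures belong to a different hypothesis. An analysis plan that followed 8.1 and 8.2 as written would inherit that.

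**Conclusion.** The point holds as a mismatch between the stated objective and the calculation that supports it, left unresolved by the analysis section. The 130 per arm is a no-difference size at 95% v 85%. At the protocol's own expected rates, its power to show non-inferiority within 10 points is about 5% in RCT-A and 14% in RCT-B, not 80%.

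The false-acceptance figure of about 13% to 18%, against about 6%, is conditional. It applies only if non-significance in the 8.1 test were taken as success, and it assumes 95% control success, a true deficit exactly at the margin, a one-sided test and 130 per arm. Two-sided tests or lower control success would give larger figures, but 8.1 states a one-sided alpha and does not use lower control rates, so they are not part of this conclusion.

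The trial is not necessarily too small. If both arms truly had 95% success, 130 per arm would be ample; the protocol does not make that assumption.

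**What to change.** 1. In section 8.2.2, replace the non-inferiority clause with a rule such as: *In each trial, non-inferiority is concluded only if the lower limit of the one-sided 95% confidence interval (equivalently, the two-sided 90% interval) for the difference in the proportion of women without symptomatic UTI at 12 months, non-antibiotic minus antibiotic, lies above −10 percentage points. A non-significant test of no difference is not evidence of non-inferiority.*

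2. In section 8.1, restate the power of 130 per arm for that rule: about 5% at 95% v 85%, 14% at 95% v 87%, and about 98% if both arms have 95% success, with the last marked as an added assumption. Do not present 80% as non-inferiority power. If a power target is kept, name the true difference, smaller than the margin, at which it applies.

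The adverse-effect sentence in 8.2.3 could be clarified, but this point does not require it.

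**Cost.** These text changes use the protocol's own margin and alpha and need no new data. Non-inferiority becomes harder to claim than under a non-significant difference test, and the stated power becomes much less favourable at the protocol's expected rates. If the sponsor wants 80% power at an expected deficit close to the margin, more women would be needed: 2483 per arm at 95% v 87%.
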